### Eligibility and baseline assessment

Once written informed consent is obtained, an eligibility assessment will be performed by the local study coordinator or staff, according to the inclusion/exclusion criteria. For each eligible participant, the following baseline characteristics will be collected: gender; age; weight; height; indications; education; nationality; registered residence (rural or urban); source (inpatient or outpatient); permanent address; *H. pylori* infection status; history of smoking and drinking; history of hypertension, diabetes, and coronary heart disease; and family history of cancer (especially oesophageal and stomach cancer). The eligibility and baseline assessment procedures will be conducted using a mobile device (tablet or phone) and web-based electronic data capture (EDC) system.

### Recruited case management

All recruited participants will be assigned identifications (IDs) comprising eight codes in the EDC system. The first four codes represent different hospitals, whereas the last four codes represent the recruiting sequences. This ID will not be used repeatedly.

### Pre-, intra-, and postoperative management

*Preoperative management* is as follows: (1) NPO for 6 h, (2) regular dosage of pronase and antifoam agent taken before examinations, (3) randomisation, (4) preoperative conversation, and (5) routine anaesthesia.

*Intraoperative management* is as follows: (1) positional nursing, lateral position; (2) insertion; (3) general method for screening upper gastrointestinal tract; (4) tissue sampling (if needed), specimen handing, and laboratory processing, and specimens will be sent to the pathology department of local study centres; (5) routine intraoperative monitoring and first-aid package preparation; and (6) intraoperative endoscopic photo documentation and report records.

*Postoperative management* is as follows: (1) routine postoperative treatment and nursing, (2) observation of vital signs in the recovery room, and (3) adverse events.

### Specimen management and pathological traceability

After tissue sampling, the specimens that arrive in the pathology department will be dehydrated, embedded, sliced, and stained. Pathological results will be obtained from local study centres by expert pathologists at each centre. Regarding patients diagnosed with gastric cancers by biopsy and those highly suspected with gastric cancer without biopsy who will possibly take further elective operations, their pathological results of resected specimens will be traced for up to 60 days from their endoscopy date to determine the invasion depth of gastric cancer.

After the training program, a group of five research assistants will watch the raw video of each participant and capture clean, high-quality frames of the lesions with pathological results under the guidance of an expert endoscopist. All images of the lesions and corresponding pathological results will be sent to an independent group of three expert endoscopists for further endoscopic evaluation. Randomisation and personal information will be concealed, and the experts will be unaware of the allocation of the lesions. A group of three experts will evaluate the endoscopic and pathological diganosis of a lesion and determine whether they are unmatched. (Here was a clerical error of describing the determination of the unmatched lesions, and we have corrected it). De-identified digital pathological slides of unmatched lesions will be sent to an independent group of expert pathologists for consultation. Only unmatched lesions will be reviewed by an independent group of expert pathologists for the final diagnosis.

Each expert pathologist is required to determine whether the slide contains acute inflammation, chronic inflammation, atrophy, or intestinal metaplasia and to rate the severity (mild, moderate, or severe) of these pathological changes. In addition, they are required to determine the presence of low-grade intraepithelial neoplasia, high-grade intraepithelial neoplasia, or carcinoma. Multiple pathological changes may occur in the same lesion, the most severe being the primary diagnosis. The severity of the pathological changes increases from inflammation to carcinoma. A lesion is diagnosed only when two or more experts reach a consensus. If the three expert pathologists did not reach a consensus, the lesion was re-evaluated until a consensus was reached.

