With the rapid progress in artificial intelligence (AI) technology, several researchers have developed intelligent systems aimed at diagnosing EGC or upper gastrointestinal neoplasms, and few studies have aimed to ensure the completeness of examinations [14, 15]. In 2019, we first applied deep learning algorithms to the field of endoscopy quality control. We developed WISENSE (renamed ENDOANGEL), an intelligent system aimed at monitoring blind spots in upper gastrointestinal endoscopy in real time [16]. Single-centre and multi-centre randomised controlled trials (RCTs) have proven to significantly reduce the blind spot rate in examinations. Furthermore, we developed ENDOANGEL-LD (lesion detection) to detect gastric abnormalities and diagnose gastric neoplasms (low-grade dysplasia, gastric adenomas, gastric lymphomas, EGC, and advanced gastric cancers) in real time [17]. In another single-centre, tandem-designed trial, we proved that ENDOANGEL-LD could reduce the biopsy rate and miss rates of gastric neoplasms in real time [18].

Development of a tool with the ability to simultaneously improve the diagnostic performance of WLE and ensure high completeness of examination is an ideal way to fulfil these needs. Therefore, we proposed the AI system ENDOANGEL-GC (gastric cancer), which simultaneously combines the functions of blind spot monitoring and lesion detection and runs in real time. We designed this randomised, controlled, patient-blinded, multi-centre trial with two parallel groups and a 1:1 allocation to evaluate the hypothesis that ENDOANGEL-GC would improve the detection rates of gastric neoplasms and EGC.

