## Outcomes

The primary outcome measures are detection rate of gastric neoplasms and EGC detection rate. The gastric neoplasm detection rate is defined as the ratio of patients with neoplasms to the recruited population. The EGC detection rate is defined as the ratio of patients with EGC to all patients with gastric cancer. EGC includes pathologically proven high-grade intraepithelial neoplasia and gastric cancer restricted to the mucosa and submucosa.

Secondary outcome measures include the detection rate of premalignant gastric lesions, biopsy rate, observation time, and number of blind spots on EGD examination. The detection rate of premalignant gastric lesions was defined as the ratio of patients with premalignant gastric lesions to the entire recruited population. The biopsy rate is defined as the ratio of patients who undergo biopsy in the recruited population. The observation time is defined as the overall examination time under WLE minus the biopsy operation time. Blind spots are defined as unobserved landmarks.

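### Lesions biopsied as low-grade neoplasia or adenoma fall outside the 60-day resection tracing, so an upgrade at resection has no stated route into the EGC primary outcome

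*Protocol article*

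**What the plan says.** All references are to the Protocol article.

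- *Specimen management and pathological traceability* names who is traced: "Regarding patients diagnosed with gastric cancers by biopsy and those highly suspected with gastric cancer without biopsy who will possibly take further elective operations". Their resection results "will be traced for up to 60 days from their endoscopy date to determine the invasion depth of gastric cancer".
- The same section keeps three grades apart when expert pathologists read a slide: "they are required to determine the presence of low-grade intraepithelial neoplasia, high-grade intraepithelial neoplasia, or carcinoma". Where one lesion shows several changes, the most severe is the primary diagnosis.
- It also provides a second look, for some lesions: "Only unmatched lesions will be reviewed by an independent group of expert pathologists for the final diagnosis".
- *Outcomes* defines the second primary outcome: "The EGC detection rate is defined as the ratio of patients with EGC to all patients with gastric cancer". It adds: "EGC includes pathologically proven high-grade intraepithelial neoplasia and gastric cancer restricted to the mucosa and submucosa".
- The *Introduction* lists what counts as a gastric neoplasm: "low-grade dysplasia, gastric adenomas, gastric lymphomas, EGC, and advanced gastric cancers".

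**The concern.** The boundary between low-grade neoplasia, high-grade neoplasia and carcinoma decides whether a patient enters the EGC ratio at all. A patient who crosses it upward joins both numerator and denominator. Yet the more definitive specimen is sought only for patients whose biopsy already shows cancer, or who were highly suspected and not biopsied. A patient whose biopsy shows low-grade neoplasia or adenoma keeps a non-cancer diagnosis even if the lesion is resected within the same 60 days and shows high-grade neoplasia or mucosal cancer.

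The error would be silent. The *Data analysis plan* excludes participants with missing pathology, but these patients have a biopsy result, so they stay in the data with the lower grade. It also need not be balanced between arms, because the plan expects more neoplasms in the experimental group.

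**Working it through.** **1. The plan's own figures reproduce** (inputs from *Sample size calculation*: EGC rate 20% vs 35%, two-sided α 0.05, power 80%, cancer in 1%, drop-out 10%).

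- Cancers per arm, unpooled Z formula: (1.960 + 0.842)² × (0.20×0.80 + 0.35×0.65) / 0.15² = 135.2. Twice this is 270.4, against the stated 270. Rounding up per arm gives 272; the pooled formula gives 276.
- Total: 270 / 0.01 / 0.90 = 30,000, as stated.

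The sample size arithmetic is therefore not in question. The point concerns the tracing rule alone.

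**2. Size of the untraced pool.** Evaluable per arm: 30,000 × 0.90 / 2 = 13,500. Cancers per arm: 1% = 135. Neoplasm rates: 2.5% control, 4.0% experimental.

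- Control: 13,500 × (0.025 − 0.010) = 202.5
- Experimental: 13,500 × (0.040 − 0.010) = 405

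This takes the same 1% cancer rate in both arms and places high-grade neoplasia within that 1%. It is an upper figure for low-grade neoplasia and adenoma, because the neoplasm definition also includes lymphoma, which cannot become EGC.

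**3. Effect on the EGC rate.** Let u be the fraction of this pool resected within 60 days and upgraded to EGC. The documents give no value, so u is an assumption. Recorded EGC counts are 0.20 × 135 = 27 and 0.35 × 135 = 47.25.

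- Control: (27 + 202.5u) / (135 + 202.5u)
- Experimental: (47.25 + 405u) / (135 + 405u)

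| u (assumed) | EGC missed, control vs experimental | Control | Experimental | Difference |
|---|---|---|---|---|
| 0 (as recorded) | 0 vs 0 | 20.0% | 35.0% | 15.0 points |
| 2% | 4 vs 8 | 22.3% | 38.7% | 16.4 points |
| 5% | 10 vs 20 | 25.6% | 43.5% | 17.9 points |
| 10% | 20 vs 41 | 30.4% | 50.0% | 19.6 points |

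With the same u in both arms, the recorded difference is too small. That direction depends on u being equal. With 10% in control and 2% in the experimental arm, the rates would be 30.4% and 38.7%, a difference of 8.2 points, and the recorded 15 would be too large.

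**4. High-grade neoplasia on biopsy.** It already counts as EGC, so only invasion beyond the submucosa would change its status. Suppose high-grade neoplasia makes up 30% to 50% of EGC and 2% to 20% of it proves that deep (both assumed). Each rate is then multiplied by 1 − (share × deep fraction).

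- Smallest case: 1 − 0.30×0.02 = 0.994, giving 19.9% vs 34.8%.
- Largest case: 1 − 0.50×0.20 = 0.90, giving 18.0% vs 31.5%.

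Power with 135 cancers per arm goes from 79% to between 79% and 73%.

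**The case against.** **The unmatched-lesion review may catch these cases.** Three endoscopists, unaware of allocation, compare the endoscopic and pathological diagnoses, and mismatches go to independent pathologists. A lesion that looks malignant but was read as low grade is an obvious candidate. This stands in part: such a lesion may be regraded, so it would be wrong to say that the local biopsy grade is always final. But the review re-reads slides, and nothing says that it retrieves a later resection.

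**The tracing sentence has a narrow purpose, and the article condenses a longer protocol.** Tracing is there to establish depth of invasion, and the text does not say that other resection results are disregarded. *Outcomes* asks for pathological proof without naming the specimen. This is fair as to detail. However, the article does state who is traced, and a site that follows that rule will not look for these specimens.

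**High-grade neoplasia may be covered.** A reader might infer that it too is plainly untraced. The documents do not settle this. *Outcomes* places it inside a ratio whose denominator is gastric cancer, which suggests that it is traced as cancer; the pathology section lists it apart from carcinoma. The effect is small on either reading.

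**The size rests on an unsourced fraction.** This stands. The value of u combines being resected, within 60 days, and upgraded, and the documents give none of the three.

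**A reader might infer that the gap manufactures a benefit for the AI system.** The documents do not support that. With equal upgrade fractions the omission works against the system; the reverse needs a markedly higher fraction in control, for which there is no evidence in the text.

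**Conclusion.** The point holds for lesions biopsied as low-grade neoplasia or adenoma. The stated tracing rule gives them no resection-based update, although their final grade decides entry to a primary outcome. The exposed pool is at most about 203 vs 405 patients, larger than the 135 cancers per arm, under the planning rates and an equal 1% cancer rate. Assumed upgrade fractions of 2% to 10%, equal between arms, raise the control rate by 2 to 10 points and the experimental rate by 4 to 15, and widen the difference from 15 to between 16 and 20 points. The true fraction, and so the true size and direction, is unknown.

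For high-grade neoplasia the finding is ambiguous wording with a small effect. The gastric neoplasm outcome is not affected by an upgrade, because a low-grade lesion already counts there. This should be corrected, but it does not invalidate the design.

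**What to change.** In *Specimen management and pathological traceability*:

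1. Extend the 60-day look-up of existing resection pathology to every participant whose biopsy shows low-grade or high-grade intraepithelial neoplasia or adenoma, as well as cancer. Apply it identically in both arms, by staff blind to allocation.
2. State that grade for the EGC outcome is the most severe diagnosis across biopsy and resection, and that depth comes from the resected specimen.
3. State that a resection showing less does not remove a biopsy-proven neoplasm. Letting the resection simply replace the biopsy would conflict with the protocol's own most-severe rule and could erase proven cases.

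Cost: a wording change, plus modest record look-up and data entry for about 600 participants (203 + 405 = 608) over the whole trial. No procedure is added and no care is altered. For participants already enrolled (more than 10,000 when the article was prepared), the look-up can be done retrospectively from existing pathology records.

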## Randomisation

Local study coordinators or staff accomplished randomisation using an EDC system. Participants were randomised into either the experimental or control group at a 1:1 ratio before the examinations. The randomisation results, time points, and case IDs will be stored online in the EDC system.

Participants will be randomised into one of the two arms by block randomisation stratified by centre. The randomisation sequence will be developed using a computer-generated random numerical series, with one encoding for the AI-assisted group and zero encoding for the control group. The original sequence will be stored in an online central randomisation system database. The online sequence will not accessible to investigators or study coordinators. If a subject fulfils the enrolment criteria, the authorised study coordinators or staff will log in to the password-protected account to obtain the assignment for him/her.

## Blinding

Patients, pathologists, and data analysts will be blinded to the randomisation. Masking of study group allocations will not attempted by the endoscopists. Randomisation results will be concealed in information brochures or other documents for the participants.

The interventions in this study will not add additional risks to participants, compared with routine sedated EGD. However, if a patient has an unexpected adverse event unrelated to the intervention and requires disclosure of study assignment information, then unblinding can be performed.

## Outcomes

The primary outcome measures are detection rate of gastric neoplasms and EGC detection rate. The gastric neoplasm detection rate is defined as the ratio of patients with neoplasms to the recruited population. The EGC detection rate is defined as the ratio of patients with EGC to all patients with gastric cancer. EGC includes pathologically proven high-grade intraepithelial neoplasia and gastric cancer restricted to the mucosa and submucosa.

Secondary outcome measures include the detection rate of premalignant gastric lesions, biopsy rate, observation time, and number of blind spots on EGD examination. The detection rate of premalignant gastric lesions was defined as the ratio of patients with premalignant gastric lesions to the entire recruited population. The biopsy rate is defined as the ratio of patients who undergo biopsy in the recruited population. The observation time is defined as the overall examination time under WLE minus the biopsy operation time. Blind spots are defined as unobserved landmarks.

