**Methods:**

*Study design*: Prospective, single-blind, parallel-group, multi-centre randomised controlled trial.

*Settings*: The computer-aided system ENDOANGEL-GC was used to monitor blind spots, detect gastric abnormalities, and identify gastric neoplasms during EGD.

*Participants*: Adults who underwent screening, diagnosis, or surveillance EGD.

Randomisation groups:

1. Experiment group, EGD examinations with the assistance of the ENDOANGEL-GC;

2. Control group, EGD examinations without the assistance of the ENDOANGEL-GC.

*Randomisation*: Block randomisation, stratified by centre.

*Primary outcomes*: Detection rates of gastric neoplasms and EGC.

*Secondary outcomes*: Detection rate of premalignant gastric lesions, biopsy rate, observation time, and number of blind spots on EGD.

*Blinding*: Outcomes are undertaken by blinded assessors.

*Sample size*: Based on the previously published findings and our pilot study, the detection rate of gastric neoplasms in the control group is estimated to be 2.5%, and that of the experimental group is expected to be 4.0%. With a two-sided α level of 0.05 and power of 80%, allowing for a 10% drop-out rate, the sample size is calculated as 4858. The detection rate of EGC in the control group is estimated to be 20%, and that of the experiment group is expected to be 35%. With a two-sided *α* level of 0.05 and power of 80%, a total of 270 cases of gastric cancer are needed. Assuming the proportion of gastric cancer to be 1% in patients undergoing EGD and allowing for a 10% dropout rate, the sample size is calculated as 30,000. Considering the larger sample size calculated from the two primary endpoints, the required sample size is determined to be 30,000.

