## Data analysis

### Sample size calculation

The sample size is calculated on the basis of the primary outcomes.

The detection rate of gastric neoplasms and EGC detection rate without AI assistance were determined by literature research. Zhang et al. reported an EGC detection rate of 20.0 to 20.9% [21] and a gastric neoplasm detection rate of 1.63%. Di et al. reported an EGC detection rate of 16.44% and a gastric neoplasm detection rate of 3.37% [22]. Therefore, the EGC detection rate in the control group is estimated to be 20%, and the gastric neoplasm detection rate is estimated to be 2.5% (the mean value of the two references).

According to our previous study, the detection rate of gastric neoplasms increased by 1.35% when assisted by an AI system; therefore, the detection rate of gastric neoplasms in the experimental group is estimated to be 4.0%. There are no published data evaluating the improvement in EGC detection rates with AI assistance. Thus, we referred to two studies reporting improvements of > 80% in EGC detection sensitivity and proportion [23, 24], resulting in an estimation that the EGC detection rate will increase from 20% to 35% with AI assistance.

The sample size was calculated, using the *Z* test method, as 4858 based on the detection rate of gastric neoplasms, with a two-sided *α* level of 0.05 and power of 80%, allowing for 10% drop-out rate. Regarding the sample size based on the EGC detection rate, the *Z* test method was used for calculation with a two-sided *α* level of 0.05 and power of 80%, resulting in a total of 270 cases of gastric cancer. Assuming the proportion of gastric cancer to be 1% in patients undergoing EGD and allowing for a 10% dropout rate, the sample size was calculated as 30,000. Considering the larger sample size calculated from the two primary endpoints, the required sample size was determined to be 30,000.

To achieve adequate participant enrolment, we first evaluated the annual volume of sedated EGD examinations at all participating centres. The sum of the examination volumes of all centres (> 20,000 per year) is sufficient to provide support for the completion of the study. In each centre, a study coordinator, group of nurses, or endoscopists will be pretrained for informed consent before the examination. Consecutive patients will be informed about the study and assessed for eligibility.

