### Data analysis plan

The analysis will use intention-to-treat (ITT) and PP approaches. The ITT population will include all patients who are randomised, whereas the PP population will include patients who undergo EGD in accordance with the assigned intervention. The null hypothesis is that the detection rates of gastric neoplasms and EGC in the experimental group will not differ from those in the control group. An alternative hypothesis is that the detection rates of gastric neoplasms and EGC in the experimental group will differ from those in the control group. The experimental group (with ENDOANGEL-GC assistance) will be compared with the control group (without ENDOANGEL-GC assistance) for the two primary outcomes using the *χ*^2^ test.

Continuous variables will be expressed as means (standard deviations [SDs]) or medians (interquartile ranges [IQRs]), according to their distributions, and categorical variables will be presented as numbers (percentages). Baseline characteristics between the two groups will be compared using the *χ*^2^ test for categorical variables and the Mann-Whitney *U* test for continuous variables. Statistical significance is set at *p* < 0.05. A 95% confidence interval will be calculated. Subgroup analysis will be conducted, stratified by multiple indices, such as age and ENDOANGEL-GC-marked red boxes, indicating that only red-box-marked lesions will be included in the analysis. The histological data and lesion characteristics will be compared with the ENDOANGEL-GC prediction, and the performance of ENDOANGEL-GC will be further analysed.

In this study, the potential missing data include the following: (1) characteristic information (the missed data will be marked with “NA” and will not be included in the analysis); (2) pathological results, the gold standards for analysis (participants with missing pathological results are excluded from the analysis); and (3) original videos (the data contained information on whether the endoscopic procedure adhered to the protocol requirements). Participants without this information will be excluded from the per-protocol analyses.

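### Two primary endpoints each take the full two-sided 0.05 and the rule for success is not stated; if either one suffices, familywise error is about 9.75%

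*Protocol article*

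**What the plan says.** The Outcomes section of the protocol article states: "The primary outcome measures are detection rate of gastric neoplasms and EGC detection rate". The first rate is taken over all recruited patients. The second is taken only over patients found to have gastric cancer.

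Each endpoint has its own sample size at the full alpha:

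- **Neoplasms** (Abstract, Methods): "With a two-sided α level of 0.05 and power of 80%, allowing for a 10% drop-out rate, the sample size is calculated as 4858". The planning rates are 2.5% for controls and 4.0% for the AI-assisted arm.
- **EGC** (Sample size calculation): two-sided alpha "level of 0.05 and power of 80%, resulting in a total of 270 cases of gastric cancer", with the planning effect "resulting in an estimation that the EGC detection rate will increase from 20% to 35% with AI assistance". The conversion to patients is made "Assuming the proportion of gastric cancer to be 1% in patients undergoing EGD and allowing for a 10% dropout rate".

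The same section then takes the larger of the two: "Considering the larger sample size calculated from the two primary endpoints, the required sample size was determined to be 30,000".

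The Data analysis plan compares the arms on both primary outcomes by a chi-square test. Its single threshold reads "Statistical significance is set at *p* < 0.05". One null and one alternative hypothesis are given, each covering both rates in one sentence joined by the word and. No section states a hierarchy, an alpha split, or whether success means both endpoints or one.

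**The concern.** With two primary tests, the error rate of the trial's main conclusion depends on how the two results are combined, and the protocol does not say how.

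The hypotheses do not settle it. Read literally, the joint null (neither rate differs) is false as soon as one rate differs, so one significant test would reject it. The stated alternative is that both rates differ. The two statements are not complementary, and a mixed result, with one endpoint significant and the other not, has no verdict. Nothing written would stop such a result being reported as a positive trial, and the false-positive rate of that claim would exceed the 5% used for planning.

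The matter is most acute for EGC. The Sample size calculation acknowledges that no published data exist on AI improvement of this rate, and the test rests on about 270 cancers.

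**Working it through.** **Inputs.** Neoplasm rates 2.5% v 4.0%; EGC rates 20% v 35% among gastric cancers; two-sided alpha 0.05; power 80%; gastric cancer in 1% of patients; dropout 10%; allocation 1:1 (Abstract, Sample size calculation, Randomisation).

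**1. Which alpha do the stated sizes use?** Unpooled Z formula, per arm: n = (z₁₋α/₂ + z₁₋β)² × [p₁(1−p₁) + p₂(1−p₂)] / (p₂−p₁)², with (1.960 + 0.842)² ≈ 7.849.

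- Neoplasms: 7.849 × 0.062775 / 0.000225 ≈ 2189.8 per arm, 4379.7 in total; divided by 0.9 ≈ 4866. The pooled version gives 2193 per arm, 4386 in total, 4874 after dropout. Both lie within 1% of the stated 4858.
- EGC: 7.849 × 0.3875 / 0.0225 ≈ 135.2 per arm, about 270 cancers, as stated (276 pooled). Then 270 / 0.01 / 0.9 = 30,000, exactly as stated.

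At alpha 0.025 each, the sizes would be about 5,902 patients (pooled) for neoplasms and 328 (unpooled) to 336 (pooled) cancers for EGC. In patients, the EGC requirement would be 328 / 0.01 / 0.9 ≈ 36,400 to 336 / 0.01 / 0.9 ≈ 37,300. So the plan gives each endpoint the full 0.05.

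**2. Error if either endpoint suffices, both nulls true.**

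- Independent tests: 1 − 0.95² = 9.75%; upper bound 0.05 + 0.05 = 10%.
- Improvement only: 1 − 0.975² = 4.94%, against a nominal 2.5%.
- The documents give no correlation between the tests. Over an assumed range, the two-sided figure is 9.6% at 0.2, 9.1% at 0.5 and 7.8% at 0.8.
- Simulation (400,000 runs, 13,500 evaluable per arm; assumed 2.5% neoplasms, 40% of them cancer, which is 1% / 2.5%, and 20% of cancers early): 9.7% two-sided, 4.9% for improvement only, correlation about 0. Near-independence is expected, because the EGC rate is conditional on having gastric cancer.

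**3. Error if both are required.** A false claim needs a false rejection of at least one true null tested at 0.05, so the error is at most 5% without adjustment.

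**4. What each remedy costs.** Evaluable patients per arm: 30,000 × 0.9 / 2 = 13,500.

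- Neoplasm power at 0.05: 0.9999997 for 2.5% v 4.0%. With the 1.35-point gain cited from the earlier study (2.5% v 3.85%) it is about 0.99999.
- EGC power at 135 cancers per arm, pooled formula: 79% at alpha 0.05, 70% at 0.025.
- Fixed sequence, neoplasms first: familywise error at most 5%; EGC power stays at about 79%.
- Both required: joint power is at least 0.791 + 0.9999997 − 1 ≈ 79%.
- Equal split: familywise error 1 − 0.975² = 4.94%, but EGC power drops to 70% unless the trial grows as in step 1.

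**The case against.** **The documents may intend both endpoints.** The Introduction states one hypothesis covering both rates, the Data analysis plan joins them in the null and in the alternative, and the larger sample size was taken, which is what one does when both endpoints must be powered. Under that rule 0.05 on each test is correct. This stands as a possible reading, but no section states it.

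**The analysis plan may settle it.** A statistical analysis plan is not shown, and a testing order is often set there. In part this stands: full alpha on each test is compatible with a both-required rule or a fixed sequence, and no written number has to change. But the protocol has already committed the alpha. An equal split added later would contradict the sample size section and cut EGC power, so only some rules remain open, and the article names none of them.

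**The threshold is general.** The 0.05 sentence follows the baseline comparisons and is not a decision rule for the primary endpoints. That is fair, but the sample size section uses the same level for each endpoint.

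**The harm is remote on the plan's own assumptions.** With neoplasm power above 99.99%, a lone EGC success would almost never occur. That is right. The protection matters if the true neoplasm effect is absent or far smaller than planned, which is when control of false claims is needed.

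**Conclusion.** The point holds in conditional form. The protocol names two primary endpoints, sizes and tests each at two-sided 0.05, and leaves the success rule unstated. If either endpoint suffices, familywise error is about 9.75% two-sided, or about 4.9% against 2.5% for false improvement claims. If both are required, it is at most 5%.

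A reader might infer that the trial simply has a false-positive rate of nearly 10%. The documents do not support that. The figure needs three conditions: that one significant endpoint is enough, that neither rate truly differs, and that results favouring control count as claims. The first is nowhere stated, and the joint wording and the larger sample size fit the opposite rule equally well.

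It is still more than a missing detail. As written, a lone significant result on either primary endpoint could be claimed with familywise error uncontrolled.

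**What to change.** Amend the Outcomes section and the Data analysis plan, before unblinded results exist, to state the success rule. Two options keep both alphas and the 30,000 patients:

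- **Both required.** The trial is positive only if both endpoints are significant at two-sided 0.05. Cost: a significant neoplasm result alone would not make the trial positive. With EGC power near 80%, that would happen about one time in five under the plan's assumptions.
- **Fixed sequence, if separate claims are wanted.** Test gastric neoplasm detection in the ITT population at two-sided 0.05, and test EGC at two-sided 0.05 only if the first is significant. The population must be named because the section lists both ITT and per-protocol analyses. Cost: no confirmatory EGC claim if the neoplasm test fails, which is likely only if the true neoplasm effect is absent or far smaller than planned.

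Either option takes about one sentence. The hypotheses should be reworded to match the rule chosen. An equal alpha split is also valid, but it would need about 36,400 to 37,300 patients to keep 80% power for EGC.
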